## Activity

When at home, subjects should maintain their usual activities from the time they sign the informed consent form to the final follow-up visit. They will abstain from strenuous exercise for 48 hours prior to each blood collection for clinical laboratory tests. Subjects may participate in light recreational activities during studies (e.g., watch television, read*).*

# Concomitant Medications and Non-Drug Therapies

## Permitted Medications

Paracetamol at doses of ≤ 2 grams/day is permitted as well as Ibuprophen ≤ 1200 mg/day. Other concomitant medication may be considered on a case by case basis by the GSK Medical Monitor.

Stable regimens of aspirin, ACE inhibitors, beta-blockers, calcium channel blockers, thyroid replacement hormone, and HMG-CoA reductase inhibitors (statins) will be allowed if their dose regimen(s) remain constant throughout the study period. Statins are not expected to alter bile acid excretion directly, but their effects on cholesterol metabolism may indirectly reduce the concentration of bile acids in faeces.

## Prohibited Medications

Subjects must abstain from taking prescription or non-prescription drugs (including vitamins and dietary or herbal supplements), within 7 days (or 14 days if the drug is a potential enzyme inducer) or 5 half-lives (whichever is longer) prior to the first dose of study medication until completion of the follow-up visit, unless in the opinion of the Investigator and sponsor the medication will not interfere with the study.

Paracetamol should not be used in patients with acute viral hepatitis.

## Non-Drug Therapies

Subjects must abstain from taking any vitamins, herbal and dietary supplements within 7 days (or 14 days if the drug is a potential enzyme inducer) or 5 half-lives (whichever is longer) prior to the first dose of study medication until completion of the follow-up visit, unless in the opinion of the Investigator and sponsor the medication will not interfere with the study.

## Medical Devices

There are no GSK manufactured medical devices (or devices manufactured for GSK by a third party) provided for use in this study

There are however other medical devices (not manufactured by or for GSK) provided for use in this study are the EnteroTest (HDC Corporation (Milpitas, USA).

Instructions for medical device use are provided in the SPM.

# completion or early withdrawal of subjects

## Subject Completion

A completed subject is one who has completed all phases of the study including the follow-up visit.

The end of the study is defined as the last subject’s last visit, in this case the follow-up visit.

## Subject Withdrawal Criteria

A subject may withdraw from the study at any time at his/her own request, or may be withdrawn at any time at the discretion of the investigator for safety, behavioural or administrative reasons.

## Subject Withdrawal Procedures

Follow-up procedures will be conducted when a subject is withdrawn or withdraws from the study.

### Subject Withdrawal from Study

A subject may withdraw from the study at any time at their own request, or they may be withdrawn at any time based on general safety and tolerability.

If a subject is prematurely discontinued from participation in the study for any reason, the investigator will make every effort to perform the following evaluations: physical examination, vital signs (blood pressure and heart rate), clinical chemistry, haematology, urinalysis, serum/urine pregnancy test (if applicable) and AE assessment. These data will be recorded, as they comprise an essential evaluation that needs to be done before discharging any subject from the study. The reason for withdrawal or failure to provide a reason must be documented by the investigator on the Completion/Withdrawal Section of the Case Report Form (CRF).

Subjects who prematurely discontinue the study may be replaced; this will be evaluated on a case by case basis.

## Treatment After the End of the Study

Subjects will not receive any additional treatment after completion of the study because they will return to their previously prescribed metformin medication.

## Screen and Baseline Failures

Data for screen and baseline failures will not be collected.

# Adverse Events (AE) and Serious Adverse Events (SAE)

The investigator or site staff are responsible for detecting, documenting and reporting events that meet the definition of an AE or SAE.

AEs will be collected from the start of the study and until the follow-up contact. Medical occurrences that begin prior to the start of investigational product but after obtaining informed consent may be recorded on the Medical History/Current Medical Conditions CRF.

SAEs will be collected over the same time period as stated above for AEs. However, any SAEs assessed as related to study participation (e.g. investigational product, protocol-mandated procedures, invasive tests, or change in existing therapy) or related to a GSK concomitant medication will be recorded from the time a subject consents to participate in the study up to and including any follow-up contact. All SAEs will be recorded and reported to GSK within 24 hours, as indicated in Section 11.7.

Investigators are not obligated to actively seek AEs or SAEs in former study participants. However, if the investigator learns of any SAE, including a death, at any time after a subject has been discharged from the study, and he/she considers the event reasonably related to the investigational product or study participation, the investigator would promptly notify GSK.

## Definition of Adverse Events

An AE is any untoward medical occurrence in a patient or clinical investigation subject, temporally associated with the use of a medicinal product, whether or not considered related to the medicinal product.

Note: An AE can therefore be any unfavourable and unintended sign (including an abnormal laboratory finding), symptom, or disease (new or exacerbated) temporally associated with the use of a medicinal product.

Events meeting the definition of an AE **include**:

- Any abnormal laboratory test results (haematology, clinical chemistry, or urinalysis) or other safety assessments (e.g.,, radiological scans, vital signs measurements), including those that worsen from baseline, and felt to be clinically significant in the medical and scientific judgement of the investigator.
- Exacerbation of a chronic or intermittent pre-existing condition including either an increase in frequency and/or intensity of the condition.
- New conditions detected or diagnosed after investigational product administration even though it may have been present prior to the start of the study.
- Signs, symptoms, or the clinical sequelae of a suspected interaction.
- Signs, symptoms, or the clinical sequelae of a suspected overdose of either investigational product or a concomitant medication (overdose per se will not be reported as an AE/SAE).
- "Lack of efficacy" or "failure of expected pharmacological action" per se will not be reported as an AE or SAE. However, the signs and symptoms and/or clinical sequelae resulting from lack of efficacy will be reported if they fulfil the definition of an AE or SAE.
- The signs and symptoms and/or clinical sequelae resulting from lack of efficacy will be reported if they fulfil the definition of an AE or SAE. Also, "lack of efficacy" or "failure of expected pharmacological action" also constitutes an AE or SAE.

Events that **do not** meet the definition of an AE include:

- Any clinically significant abnormal laboratory findings or other abnormal safety assessments that are associated with the underlying disease, unless judged by the investigator to be more severe than expected for the subject’s condition.
- The disease/disorder being studied, or expected progression, signs, or symptoms of the disease/disorder being studied, unless more severe than expected for the subject’s condition.
- Medical or surgical procedure (e.g., endoscopy, appendectomy); the condition that leads to the procedure is an AE.
- Situations where an untoward medical occurrence did not occur (social and/or convenience admission to a hospital).
- Anticipated day-to-day fluctuations of pre-existing disease(s) or condition(s) present or detected at the start of the study that do not worsen.

## Definition of Serious Adverse Events

If an event is not an AE per Section 11.1, then it cannot be an SAE even if serious conditions are met (e.g., hospitalization for signs/symptoms of the disease under study, death due to progression of disease, etc).

An SAE is any untoward medical occurrence that, at any dose:

1. Results in death
2. Is life-threatening

NOTE: The term 'life-threatening' in the definition of 'serious' refers to an event in which the subject was at risk of death at the time of the event. It does not refer to an event, which hypothetically might have caused death, if it were more severe.

1. Requires hospitalization or prolongation of existing hospitalisation

NOTE: In general, hospitalisation signifies that the subject has been detained (usually involving at least an overnight stay) at the hospital or emergency ward for observation and/or treatment that would not have been appropriate in the physician’s office or out‑patient setting. Complications that occur during hospitalisation are AEs. If a complication prolongs hospitalisation or fulfils any other serious criteria, the event is serious. When in doubt as to whether “hospitalisation” occurred or was necessary, the AE should be considered serious.

Hospitalization for elective treatment of a pre-existing condition that did not worsen from baseline is not considered an AE.

1. Results in disability/incapacity, or

NOTE: The term disability means a substantial disruption of a person’s ability to conduct normal life functions. This definition is not intended to include experiences of relatively minor medical significance such as uncomplicated headache, nausea, vomiting, diarrhea, influenza, and accidental trauma (e.g. sprained ankle) which may interfere or prevent everyday life functions but do not constitute a substantial disruption.

1. Is a congenital anomaly/birth defect
2. Medical or scientific judgment should be exercised in deciding whether reporting is appropriate in other situations, such as important medical events that may not be immediately life-threatening or result in death or hospitalization but may jeopardize the subject or may require medical or surgical intervention to prevent one of the other outcomes listed in the above definition. These should also be considered serious. Examples of such events are invasive or malignant cancers, intensive treatment in an emergency room or at home for allergic bronchospasm, blood dyscrasias or convulsions that do not result in hospitalization, or development of drug dependency or drug abuse.
3. Is associated with liver injury **and** impaired liver function defined as:

- ALT ≥ 3xULN, and
- total bilirubin ≥ 2xULN or INR > 1.5.

**NOTES:**

Bilirubin fractionation should be performed if testing is available. If fractionation is unavailable, urinary bilirubin is to be measured via dipstick (a measurement of direct bilirubin, which would suggest liver injury).

INR measurement is not required; if measured, the threshold value stated will not apply to patients receiving anticoagulants. If INR measurement is obtained, the value is to be recorded on the SAE form.

## Method of Detecting AEs and SAEs

Care will be taken not to introduce bias when detecting AEs and/or SAEs. Open-ended and non-leading verbal questioning of the subject is the preferred method to inquire about AE occurrence. Appropriate questions include:

Care will be taken not to introduce bias when detecting AEs and/or SAEs. Open-ended and non-leading verbal questioning of the subject is the preferred method to inquire about AE occurrence. Appropriate questions include:

- “How are you feeling?”
- “Have you had any (other) medical problems since your last visit/contact?”
- “Have you taken any new medicines, other than those provided in this study, since your last visit/contact?”

## Recording of AEs and SAEs

When an AE/SAE occurs, it is the responsibility of the investigator to review all documentation (e.g., hospital progress notes, laboratory, and diagnostics reports) relative to the event. The investigator will then record all relevant information regarding an AE/SAE in the appropriate data collection tool.

It is not acceptable for the investigator to send photocopies of the subject’s medical records to GSK in lieu of completion of the GSK, AE/SAE data collection tool. However, there may be instances when copies of medical records for certain cases are requested by GSK. In this instance, all subject identifiers, with the exception of the subject number, will be blinded on the copies of the medical records prior to submission of to GSK.

The investigator will attempt to establish a diagnosis of the event based on signs, symptoms, and/or other clinical information. In such cases, the diagnosis will be documented as the AE/SAE and not the individual signs/symptoms.

Subject-completed health outcomes questionnaires and the collection of AE data are independent components of the study. Responses to each question in the health outcomes questionnaire will be treated in accordance with standard scoring and statistical procedures detailed by the scale’s developer. The use of a single question from a multidimensional health survey to designate a cause-effect relationship to an AE is inappropriate.

## Evaluating AEs and SAEs

### Assessment of Intensity

The investigator will make an assessment of intensity for each AE and SAE reported during the study and will assign it to one of the following categories:

Mild: An event that is easily tolerated by the subject, causing minimal discomfort and not interfering with everyday activities.

Moderate: An event that is sufficiently discomforting to interfere with normal everyday activities.

Severe: An event that prevents normal everyday activities.

An AE that is assessed as severe will not be confused with an SAE. Severity is a category utilized for rating the intensity of an event; and both AEs and SAEs can be assessed as severe. An event is defined as ‘serious’ when it meets at least one of the pre-defined outcomes as described in the definition of an SAE.

### Assessment of Causality

The investigator is obligated to assess the relationship between investigational product and the occurrence of each AE/SAE. A "reasonable possibility" is meant to convey that there are facts/evidence or arguments to suggest a causal relationship, rather than a relationship cannot be ruled out. The investigator will use clinical judgment to determine the relationship. Alternative causes, such as natural history of the underlying diseases, concomitant therapy, other risk factors, and the temporal relationship of the event to the investigational product will be considered and investigated. The investigator will also consult the Investigator Brochure (IB) and/or Product Information, for marketed products, in the determination of his/her assessment.

There may be situations when an SAE has occurred and the investigator has minimal information to include in the initial report to GSK. However, **it is very important that the investigator always make an assessment of causality for every event prior to the initial transmission of the SAE data to GSK.** The investigator may change his/her opinion of causality in light of follow-up information, amending the SAE data collection tool accordingly. The causality assessment is one of the criteria used when determining regulatory reporting requirements.

## Follow-up of AEs and SAEs

After the initial AE/SAE report, the investigator is required to proactively follow each subject at subsequent visits/contacts. All AEs and SAEs will be followed until resolution, until the condition stabilizes, until the event is otherwise explained, or until the subject is lost to follow-up.

The investigator is obligated to perform or arrange for the conduct of supplemental measurements and/or evaluations as may be indicated or as requested by GSK to elucidate as fully as possible the nature and/or causality of the AE or SAE. The investigator is obligated to assist. This may include additional laboratory tests or investigations, histopathological examinations or consultation with other health care professionals. If a subject dies during participation in the study or during a recognized follow-up period, the investigator will provide GSK with a copy of any post-mortem findings, including histopathology. New or updated information will be recorded in the originally completed data collection tool. The investigator will submit any updated SAE data to GSK within the designated reporting time frames.

## Prompt Reporting of SAEs to GSK

Once the investigator determines that an event meets the protocol definition of an SAE, the SAE will be reported to GSK **within 24 hours**. Any follow-up information on a previously reported SAE will also be reported to GSK within 24 hours.

If the investigator does not have all information regarding an SAE, he/she will not wait to receive additional information before notifying GSK of the event and completing the appropriate data collection tool. The investigator will always provide an assessment of causality at the time of the initial report as described in Section 11.5.2, Assessment of Causality.

The primary mechanism for reporting SAEs to GSK will be the electronic data collection tool (e.g., PIMS).If the electronic system is unavailable for greater than 24 hours; the site will use the paper SAE data collection tool and fax it to the GSK Medical Monitor. Then the site will enter the serious adverse event data into the electronic system as soon as it becomes available.

After the study is completed at a given site, the electronic data collection tool (e.g., PIMS system) will be taken off-line to prevent the entry of new data or changes to existing data. If a site receives a report of a new SAE from a study participant or receives updated data on a previously reported SAE after the electronic data collection tool has been taken off-line, the site can report this information on a paper SAE form or to their GSK protocol contact by telephone.

GSK contacts for SAE receipt can be found at the beginning of this protocol on the Sponsor/Medical Monitor Contact Information page.

Facsimile transmission of the SAE data collection tool is the preferred method to transmit this information to the project contact for SAE receipt. In rare circumstances and in the absence of facsimile equipment, notification by telephone is acceptable, with a copy of the SAE data collection tool sent by overnight mail. Initial notification via the telephone does not replace the need for the investigator to complete and sign the SAE data collection tool within the designated reporting time frames.

GSK contacts for SAE receipt can be found at this beginning of this protocol on the Sponsor/Medical Monitor Contact Information page.

Facsimile transmission of the following PIMS listings for the corresponding subject is the preferred method to transmit SAE information to the GSK Medical Monitor or protocol contact:

- SAE listing
- Demographic listing
- Investigational product listing

In rare circumstances and in the absence of facsimile equipment, notification by telephone is acceptable, with a copy of all required information sent by overnight mail.

If the PIMS system is unavailable when the SAE occurs, the site will use the paper SAE form and fax that to the GSK medical Monitor or protocol contact. The site will enter the SAE data into PIMS as soon as the system becomes available.

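### Section 11.7 gives two conflicting triggers for the paper SAE report, and one of them (more than 24 hours of system outage) does not fit the protocol's own 24-hour deadline

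*Protocol*

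**What the plan says.** Section 11 sets the deadline: "All SAEs will be recorded and reported to GSK within 24 hours, as indicated in Section 11.7". Section 11.7 repeats the limit and starts the clock: "Once the investigator determines that an event meets the protocol definition of an SAE, the SAE will be reported to GSK", again within 24 hours. It applies the same limit to later information: "Any follow-up information on a previously reported SAE will also be reported to GSK within 24 hours".

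On the route, Section 11.7 says: "The primary mechanism for reporting SAEs to GSK will be the electronic data collection tool", with PIMS as the example. It then gives two rules for an outage:

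- **Rule A**, directly after the primary mechanism: "If the electronic system is unavailable for greater than 24 hours; the site will use the paper SAE data collection tool", which is faxed to the Medical Monitor.
- **Rule B**, at the end of the section: "If the PIMS system is unavailable when the SAE occurs, the site will use the paper SAE form", which is faxed to the Medical Monitor or protocol contact.

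Under both rules the site enters the data electronically once the system is back. Between them stands a sentence with no outage condition: "Facsimile transmission of the SAE data collection tool is the preferred method to transmit this information". Telephone notification is accepted in rare circumstances where there is no fax equipment, with a copy to follow by overnight mail.

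**The concern.** A fallback exists so that the deadline can be met when the main route fails. Rule A opens the fallback only after more than 24 hours of outage, and the deadline is itself 24 hours. For an outage that starts once the clock is running, the paper route therefore opens after the report was due. Rule B, in the same section, tells the site to use paper without waiting. A site cannot tell from the text which sentence governs.

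At stake is the timeliness of safety notification. Section 11.8 calls prompt notification essential to the sponsor's legal and ethical duties, and Section 13.2.1 provides for urgent safety measures when a new event is likely to affect subjects' safety. Subjects spend the washout at home without metformin, so an SAE may occur some time before the investigator learns of it and classifies it.

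**Working it through.** The protocol gives no figure to reproduce. The check is a timeline, followed by a comparison of what each rule covers.

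**Inputs**
- Deadline: 24 hours (Sections 11 and 11.7).
- Hour 0: the investigator's determination that the event is an SAE (Section 11.7).
- Rule A: paper opens after more than 24 hours of outage.
- Rule B: paper opens at once if PIMS is down when the SAE occurs.
- Assumption: the electronic system of Rule A and the PIMS system of Rule B are the same.

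**Rule A alone.** Let the outage start at hour s, negative if before the determination. Paper opens after hour s + 24.

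| Outage starts (s) | Paper opens after hour s + 24 | Can the 24-hour deadline be met? |
| --- | --- | --- |
| −20 | −20 + 24 = 4 | Yes, 24 − 4 = 20 hours remain |
| −6 | −6 + 24 = 18 | Yes, 24 − 18 = 6 hours remain |
| 0 | 0 + 24 = 24 | Not on paper; only if the system recovers by hour 24 |
| +6 | 6 + 24 = 30 | Not on paper; only if filed electronically in the first 6 hours or the system recovers by hour 24 |

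Rule A therefore forces a late report when three conditions hold together: s is 0 or more, the report was not filed before the outage began, and the outage is still running at hour 24. The outage need not exceed 24 hours. With s = +6, one of 20 hours ends at hour 6 + 20 = 26. Rule A never opens paper, and the electronic report is at least 26 − 24 = 2 hours late.

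**Rule B on the same timeline.** If PIMS is down when the SAE occurs, paper is available from hour 0 and the deadline can be met.

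**What Rule B leaves open**
1. Its trigger is the state of the system when the SAE occurs, whereas the clock starts at the determination. If PIMS is up when the event occurs at home and down when it is classified, Rule B does not literally apply and Rule A does.
2. An outage that begins after the SAE occurs is outside its wording for the same reason.
3. It says nothing of follow-up information, which carries the same 24-hour limit.

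In these cases the site has only Rule A and the general fax and telephone wording.

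**The case against.** The strongest reply is that the deadline is never relaxed. Section 11 states it and Section 11.7 repeats it. Rule A chooses a tool and does not say that the report may wait. A careful site would comply through Rule B or the fax and telephone wording. This stands as far as it goes, and it rules out several stronger readings that a reader might infer:

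- *That paper is available only after 24 hours of outage.* That is true of Rule A but not of Section 11.7 as a whole, because Rule B has no wait.
- *That following Rule A always means a late report.* An outage that began early enough before the determination, or a system that recovers in time, leaves an on-time route.
- *That three rival triggers are in force.* The fax sentence has no outage trigger. It comes shortly after the paragraph on reports received once the tool has been taken off-line, and may refer to those. The next fax sentence concerns PIMS listings and may complement electronic entry. Only Rules A and B conflict as triggers.
- *That protective action for other subjects in washout would be delayed.* This is not shown. The study runs at the sponsor's own clinical unit with approximately 16 subjects, and staff aim for daily contact. Section 13.2.1 assigns urgent measures to the investigator as well as the sponsor, so the investigator need not wait for a form.

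The reply does not remove the conflict. Rule B misses the cases listed above, and a site should not have to decide which of two instructions in a mandatory reporting section to disregard.

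**Conclusion.** The point holds as a wording conflict in safety reporting. Section 11.7 contains two inconsistent triggers for the paper form, and the one based on more than 24 hours of outage does not fit the 24-hour deadline. It produces a late report only under the three conditions shown above, for a site that acts on that sentence alone. Rule B narrows the problem without closing it.

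The conclusion rests on the literal wording and on treating the two named systems as one. The protocol gives neither the frequency nor the length of outages, so no rate of late reports can be stated. No endpoint, estimate or analysis is affected. The defect is small, but it sits in a mandatory rule and costs almost nothing to correct.

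**What to change.** In Section 11.7, delete the condition that the outage must exceed 24 hours, and merge the two fallback sentences into one rule. For example: *The electronic tool is the primary route. If it is unavailable when an initial or follow-up SAE report is due, the site sends the paper form by fax, or notifies by telephone if there is no fax equipment, within the same 24 hours, and enters the data electronically when the system returns.* Tying the rule to when a report is due, and no longer to when the SAE occurs, covers later outages and follow-up information.

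The sentences that call fax the preferred method need not be removed. They should be made consistent with the electronic tool as primary route, for instance by saying whether they apply to the paper form, to the PIMS listings, or to reports made after the tool is off-line.

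The cost is a short text edit and occasional double entry of an SAE during brief outages.
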